**Figure 1 F1:**
[figure not shown]
**The fear-avoidance belief model (Vlayen & Linton **[35]**).**

#### **
*Targets for a multidisciplinary CBT intervention for patients undergoing LSF surgery*
**

Summarizing the theoretical background and the research described above, the targets of the intervention should encompass the following basic components.

• The first component aims to increase the patient’s knowledge about pain and pain perception in order to gain a better understanding of how cognitions and behaviour affect the pain experience. It emphasizes the role that the patient can play in controlling his or her own pain.

• The second component relates to the use of active coping skills. Skills training may use a variety of cognitive and behavioural pain-coping strategies, such as activity pacing and pleasant activity scheduling. Catastrophic pain-related thoughts are challenged by formulating more realistic appraisals using cognitive restructuring techniques.

• The third component involves the application and maintenance of learned coping skills. The patients are now encouraged to try out the learned coping skills to an increasingly wider range of daily situations.

• The fourth component focuses on problem-solving methods that enable the patients to analyse and develop plans for dealing with pain flares and other challenging situations.

## Methods/Design

### Trial design

The study is a randomized clinical trial with 1-year follow-up.

### Participants

Patients eligible for inclusion were persons at the age of 18–64 years scheduled for lumbar spinal fusion surgery (maximum of 3 adjacent vertebrae) due to pain and disability as a consequence of degenerative diseases or spondylolisthesis grade 1 or 2. Patients were included from two hospitals in the same uptake area covering 1,272,510 inhabitants.

### Interventions

#### **
*Control group*
**

Patients in the control group received usual care, being the department's standard care related to their surgical procedure. In one of the hospitals usual care included a voluntary information meeting for patients and their spouses/relatives, approximately 2 weeks prior to surgery. Patients were routinely called for a control visit with the operating surgeon at 3 and 12 months. Following the 3 months control visit, patients commenced physical rehabilitation in their local community (e.g. physical therapy clinic or rehabilitation centre). This typically consists of 1–2 individual sessions followed by 10 sessions of supervised group-based exercise.

#### **
*Intervention group*
**

In addition to the described usual care (surgery and physical rehabilitation), patients in the intervention group participated in a patient education using a cognitive-behavioural therapy (CBT) approach.

##### 

**Structure** The CBT intervention consisted of six sessions, each of three hours duration. Patients were to attend four of the sessions prior to surgery, while the fifth and sixth sessions were placed postoperatively, at three and six months respectively. The length of the intervention was designed to optimize attendance with the time required to develop the needed skills. A previous study found no difference in outcome between programs of 15, 30 or 60 hours duration [38]. A group format was used for the intervention, as evidence suggests that there is no difference in outcome between individual and group therapy [39].

##### 

**Setting** The six sessions of the patient education took place in a conference room at the hospital, where most of the patients were to undergo surgery. The room was placed in an administrative building and hence did not have the look of a typical hospital ward. The room was big enough for the participants to move around, sit or stand as they pleased.

##### 

**The multidisciplinary team** The health professionals delivering the intervention were a psychologist, an occupational therapist, a physiotherapist, a spine surgeon, a social worker and an experienced patient. The psychologist and occupational therapist both attended the sessions most of the time, and one or the other was always present at the attendance of the other health professionals. The focus of their roles concerned the presentation of a unified message rather than the maintenance of traditional professional boundaries. The surgeon and the two therapists were affiliated to the surgical department at the hospital where the intervention took place, and all had several years of experience with LSF patients. The psychologist and social worker both had several years of experience with multidisciplinary treatment of chronic back pain patients in a hospital setting. The team participated in a 2-day training program, covering the risk factors associated with chronic pain, the CBT model, developing basic CBT skills including questioning techniques, and learning the topics to be covered in each session. Training was delivered by the psychologist participating in the intervention. Furthermore an intervention manual forming the intervention guidelines was developed in order to standardize the intervention as much as possible.

##### 

**Content** The content of each session was pre-specified with some flexibility to respond to participants’ needs. Details of each session are presented in Table 1. The key elements of the contents of each session were summarized in a patient handbook handed out the patient’s first attendance. The post-operative sessions focused on recapitulation of the CBT tools learned at the preoperative sessions, and how they could be used in the rehabilitation process after the operation. There was left sufficient time for patients to discuss worries and unexpected up- and downturns after the operation, and to share their individual experiences regarding the learned pain coping strategies with fellow patients. The slide show used in the group sessions, the patient handbook and the intervention manual can be retrieved by contacting the first author of this paper.

**Table 1 T1:** Contents of each of the six sessions

** *All sessions commence with a short presentation of the day's session, new participants are introduced, and homework and questions from the previous session are discussed.* **	
	**Session A – preoperative**
**CBT**	Physical and psychological reactions in stressful situations.
	The link between thoughts, feelings, bodily reactions and behaviour.
**Preparing for surgery**	What to expect of the operation and the postoperative course.
**Homework**	Identify and write down thoughts and feelings in relation to painful or stressful situations. Consider and write down alternative and realistic thoughts.
	**Session B – preoperative**
**CBT**	Causes and consequences of pain. The fear-avoidance belief model and the importance of physical activity in reducing pain.
**Preparing for surgery**	Pleasant activity scheduling and activity pacing.
	Ergonomics - working posture following surgery.
**Homework**	Identify and write down 3 activities you used to enjoy. Plan and go through with them considering your pain level. How did it affect your mood and pain level?
	**Session C – preoperative**
**CBT**	The link between thoughts, feelings, bodily reactions and behaviour.
	Negative automatic thoughts and their role in maintenance of a vicious circle.
	Active and passive coping strategies.
**Homework**	Identify and write down your own coping strategies when in pain and distress.
	Try to use active coping strategies. How did it affect your pain level?
	**Session D – preoperative**
**CBT**	How to cope with pain and distress in relation to family, friends and work.
**Preparing for surgery**	The experiences of a previously operated patient.
	Legislation and procedures in the authorities when being on sick leave and in relation to return to work.
**Homework**	Say no to 3 tasks, that you would usually agree to do, despite not being comfortable doing it.
	Promt a friend, colleague or family to give you a positive support remark.
	Give a friend, colleague or family a positive remark and notice the reaction.
	**Follow-up session 1 – postoperative (3 months)**
**CBT**	Reflection of how patients have used the acquired cognitive techniques and coping strategies postoperatively.
	Using pacing techniques to restart daily activities, hobbies and work.
**Homework**	Goal setting for the next three months.
	Use pacing techniques to achieve one or more of your goals.
	**Follow-up session 2 – postoperative (6 months)**
**CBT**	Reflection of how patients have used the acquired cognitive techniques and coping strategies during the past 3 months.
	Discussion of achievements of previously set goals. Setting future goals.
	Coping with flare-ups.
	Returning to work – expectations, worries and how to cope with barriers.

### Outcomes

For each patient baseline characteristics will be registered by questionnaires or medical records: gender, age, working status, diagnosis, type of operation, comorbidity, and previous spine surgery.

#### **
*Primary outcomes*
**

– Disability (Oswestery Disability Index) [40].

– Sick-leave/Return to work.

#### **
*Secondary outcomes*
**

– Pain (Low Back Pain Rating Scale) [41].

– Quality of life (EQ-5D) [42].

– Coping strategies (Coping strategies questionnaire) [43].

– Fear-avoidance (Fear-avoidance beliefs. questionnaire) [44].

– Readmission to hospital and use of health care services.

Data concerning the patients’ use of health care service and return to work is based on self-registration [45]. Data on sick-leave compensation will be obtained from the DREAM Database, a national database administered by the Ministry of Employment.

### Sample size and data analysis

Based on a pilot study, a standard deviation of the ODI was set at 14 points on the ODI scale. A 10 points difference has been estimated as clinically relevant in a study comparing LSF with cognitive intervention [46]. Significance level was set at 0.05 and the power at 0.80. To fulfill these criteria, the study would need at total of 72 patients. With the 2:1 randomisation ratio this would mean 48 patients in the intervention group and 24 in the control group. If assuming that 10% of the included patients will be lost to follow-up, at least 80 patients should be included in the study.

All data are entered in EpiData twice. STATA 12.0 will be used for statistical evaluation. Parametric tests will be used for normally distributed data and non-parametric tests for data which are not normally distributed. Because the ODI and EQ-5D are ranked data, the Wilcoxon rank sum test will be used to test any differences between the groups within these questionnaires. The differences between numerical data (length of stay at hospital, use of health care service, physical function) will be tested with Two Sample *t*-test or Wilcoxon rank sum test. The intervention group is tested against the control group.

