### Cost effectiveness and cost utility evaluation

The economic evaluation alongside the study will be conducted as a cost-effectiveness analysis with the main parameter being ODI and incremental costs per earlier day of RTW. The EQ-5D data valued by the Danish set of preference weights will qualify as a cost-utility analysis reporting the cost per quality-adjusted life-year (QALY) [36]. The perspective of the analysis will include the primary and secondary health care sector, the patient perspective, and the societal perspective. Resource utilisation will be informed by ad hoc data collected using a modified version of the Dutch cost diary [45]. Valuation will be based on micro-costing (intervention costs), Diagnosis-Related-Grouping (DRG) tariffs (other contacts in secondary health care), the collective agreement between Local Government Denmark and primary care practitioners (contacts in primary care), market prices (patients’ costs) and national average gross salaries (production loss and time costs in general). Statistical tests will be based on precision estimates (confidence intervals) calculated using the technique of bootstrapping [47].

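### The ODI is sized as a 10-point difference in means but labelled ranked data and tested only by Wilcoxon, so the stated clinical analysis names no estimate to set against the 10-point target

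*Protocol article*

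**What the plan says.** All references are to the protocol article, under Methods/Design.

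- **Sample size and data analysis, sizing.** "Based on a pilot study, a standard deviation of the ODI was set at 14 points on the ODI scale". The target is given as "A 10 points difference has been estimated as clinically relevant in a study comparing LSF with cognitive intervention". The error rates follow: "Significance level was set at 0.05 and the power at 0.80". The result is that "the study would need at total of 72 patients", split 48 intervention and 24 control, and raised to 80 for 10% loss.
- **Sample size and data analysis, testing.** "Because the ODI and EQ-5D are ranked data, the Wilcoxon rank sum test will be used to test any differences between the groups". A separate sentence deals with numerical data, for which a t-test or a rank sum test may be used. No covariate, effect estimate or confidence interval is named for the ODI.
- **Cost effectiveness and cost utility evaluation.** The ODI is a main effect measure of the cost-effectiveness analysis. For the other score, "The EQ-5D data valued by the Danish set of preference weights will qualify as a cost-utility analysis", reported per QALY. Inference there uses bootstrap confidence intervals.
- **Outcomes.** The ODI is one of two primary outcomes. The list of baseline characteristics does not include it.
- **Participants and Interventions.** There are two hospitals. "In one of the hospitals usual care included a voluntary information meeting for patients and their spouses/relatives".

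**The concern.** The document treats the same score in two incompatible ways. If the ODI holds only rank information, a standard deviation and a 10-point difference have no clear meaning, and neither does an incremental cost per unit of ODI. If it is numerical, the reason given for choosing the Wilcoxon test falls away. The EQ-5D has the same problem, because preference-weighted values and QALYs are numerical quantities.

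This bears on a primary outcome. A rank sum p value says whether the two distributions differ. It does not say whether a 10-point benefit was reached, or, after a non-significant result, whether one was excluded. The clinical comparison and the economic evaluation could also report the ODI effect on different measures. Finally, a two-group rank sum test takes no covariates, so any precision available from a baseline score is given up unless change scores are what is tested.

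**Working it through.** **1. Reproduce the stated sample size.** Inputs from the sample size section: SD 14, difference 10, alpha 0.05, power 0.80, allocation 2:1. The article does not say whether the test is one- or two-sided; two-sided reproduces its figure.

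Control patients = (1 + 1/2) × [14 × (1.960 + 0.842) / 10]² = 23.08, rounded up to 24. With 48 intervention patients the total is 72. Allowing for loss, 72 / 0.90 = 80. Both stated figures are reproduced, and the formula is the one for a difference in means. A one-sided test would give 57 in total, and 1:1 allocation would give 62.

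**2. Power of the test that is actually planned.** The t-test figures use the noncentral t distribution. The Wilcoxon figures are simulated with normal data, SD 14 and difference 10.

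| Completers (control/intervention) | t-test | Wilcoxon |
|---|---|---|
| 24/48 | 0.804 | about 0.78 |
| 29/57 | 0.872 | about 0.85 to 0.86 |

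The second row takes the 96 patients in the Abstract with 10% loss: 96 × 0.90 = 86.4, or about 29 and 57. For 80% power the Wilcoxon test would need about 75 to 78 completers, which 96 randomised patients would supply. Power is therefore not the difficulty.

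**3. What an estimate would show.** The unadjusted 95% CI half-width at 29/57 is t × SD × √(1/29 + 1/57) = 1.989 × 14 × 0.2281 = 6.35 points. That is narrow enough to be informative against a 10-point target. The p value alone does not convey it.

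**4. What baseline adjustment could add.** The correlation r between baseline and follow-up ODI is not in the document, so it is assumed at 0.3 to 0.6. The residual SD is 14 × √(1 − r²).

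| r (assumed) | Residual SD | Power at 24/48 | CI half-width at 29/57 |
|---|---|---|---|
| 0 | 14.0 | 0.804 | 6.35 |
| 0.3 | 13.36 | 0.840 | 6.06 |
| 0.6 | 11.20 | 0.941 | 5.08 |

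**5. How much of a chance baseline imbalance reaches the result.** If the baseline SD is also 14, the standard error of the imbalance at 29/57 is 14 × 0.2281 = 3.19 points. In an unadjusted comparison of follow-up scores, with equal SDs, only r times the imbalance carries over. A one-standard-error imbalance moves the result by 0.3 × 3.19 = 1.0 to 0.6 × 3.19 = 1.9 points.

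The gain from adjusting for hospital cannot be computed from the document.

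**The case against.** The strongest defence is that the rank sum test is valid under randomisation, holds its error rate and loses only about two percentage points of power, while the trial includes 96 patients against the 80 required. Nothing here biases the primary result. That stands, and it limits the weight of the point.

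Three stronger readings are tempting, and the document does not support them.

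- *The trial gives no ODI estimate.* A reader might infer this, but the cost-effectiveness analysis needs an ODI difference and plans bootstrap intervals. A full protocol or analysis plan that is not shown may add more. Only the clinical comparison, as stated, lacks a named estimate.
- *Baseline information is discarded, so chance imbalance passes straight into the result.* The article does not list baseline ODI and does not say whether final or change scores are tested; change scores would use the baseline, though less efficiently than covariance adjustment. Even with final scores, only the fraction r of an imbalance carries over, and the unadjusted test's error rate already allows for it.
- *The difference in usual care between hospitals distorts the comparison.* The intervention group also receives the described usual care, so the difference applies to both arms. No stratification by hospital is described, so leaving hospital out contradicts nothing in the design.

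What the defence does not answer is the contradiction itself. The reason for the rank test is written in the text and conflicts with both the sizing and the economic analysis. A fuller document could add estimates, but it would not make that reason consistent.

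**Conclusion.** The point holds as an inconsistency with a practical consequence. The ODI is sized by means, called ranked when the test is chosen, and treated as numerical again in the economic evaluation. The stated clinical test cannot be read against the 10-point target.

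The consequence is loss of interpretability and, conditionally, of efficiency. The sample size is correct as calculated and the test is unbiased. The power figures assume normal data with SD 14. The adjustment gain depends on baseline ODI having been collected and on an assumed correlation of 0.3 to 0.6; at the low end the gain is slight. Severity is below an essential correction, and confidence is moderate.

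**What to change.** 1. Make the primary ODI analysis a linear model of the score at one-year follow-up on treatment group. Report the mean difference with 95% CI, using robust or bootstrap standard errors, and interpret it against 10 points. One year is taken from the stated follow-up period; the article does not name a separate time point for the ODI.
2. Adjust for baseline ODI if it was collected at inclusion, and optionally for hospital. If baseline ODI was not collected, the estimate and interval are still worth having without it.
3. Use the same approach for the EQ-5D index, so that the clinical and economic reports use one effect measure.
4. Keep the Wilcoxon test as a sensitivity analysis, and delete the sentence that justifies it by calling the scores ranked.

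The cost is a change of wording before the data are analysed and slightly more analysis work. No new data are needed; the adjustment in item 2 applies only if the baseline questionnaires exist.

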### Cost effectiveness and cost utility evaluation

The economic evaluation alongside the study will be conducted as a cost-effectiveness analysis with the main parameter being ODI and incremental costs per earlier day of RTW. The EQ-5D data valued by the Danish set of preference weights will qualify as a cost-utility analysis reporting the cost per quality-adjusted life-year (QALY) [36]. The perspective of the analysis will include the primary and secondary health care sector, the patient perspective, and the societal perspective. Resource utilisation will be informed by ad hoc data collected using a modified version of the Dutch cost diary [45]. Valuation will be based on micro-costing (intervention costs), Diagnosis-Related-Grouping (DRG) tariffs (other contacts in secondary health care), the collective agreement between Local Government Denmark and primary care practitioners (contacts in primary care), market prices (patients’ costs) and national average gross salaries (production loss and time costs in general). Statistical tests will be based on precision estimates (confidence intervals) calculated using the technique of bootstrapping [47].

### Ethical considerations

The intervention carries no risk to the patients who as a minimum are ensured the standard treatment. The study will be carried out in accordance with Declaration of Helsinki and Good Clinical Practice. The study has been approved by the Danish Protection Agency and The Ethical Committee of Central Denmark Region (journal no. M-20110047).

## Discussion

In the future an increasing proportion of older people have to live with chronic diseases. Knowledge of new interventions is required to achieve greater individual and societal gains. This project combines knowledge and evidence from different knowledge areas (biomedicine, psychology, physiotherapy and occupational therapy) because the areas isolated do not have optimal effect and because of increasing evidence of efficacy of integration of more of the areas. Further we include health economic analyses, which we hope further can provide prioritization in health and social planning. We hope that our intervention can provide better functional outcome, less pain and earlier return to work after surgery. The project is expected to provide new knowledge that can create greater consistency in patient treatment. We expect that the results can make a significant contribution to development of guidelines for good rehabilitation of patients undergoing lumbal spinal fusion. Further that new knowledge can inspire similar developments within a wide range of diseases.

## Abbreviations

LSF: Lumbar spinal fusion; CBT: Cognitive-behavioural therapy; ODI: Oswestry disability index; EQ-5D: EuroQol 5 dimensions.
